## Sample size calculation

The sample size calculation was performed considering the number of surgeries as the primary outcome, which is the main variable of interest in this clinical study. The primary analytical objective is to compare the effect of four treatment strategies on this outcome, with adjustment for age as a relevant covariate.

For sample size estimation, G*Power software version 3.1.9.6 [11] was used, as described by Kang [12], adopting the *F*-test family, specifically the ANCOVA option: fixed effects, main effects, and interactions, in an a priori analysis. This approach is widely used for comparisons between groups with adjustment for covariates in clinical studies [13–15]. A medium effect size (*f* = 0.25), a significance level of 5% (*α* = 0.05), and a statistical power of 80% (1 − *β* = 0.80) were assumed, as recommended to ensure adequate ability to detect clinically relevant differences. The model included four comparison groups and one covariate (age). Based on these parameters, a minimum total sample size of 179 participants was estimated. Assuming a 10% loss to follow-up, the total sample size would be approximately 200 participants, corresponding to about 50 individuals per group, resulting in a test with degrees of freedom *F*(3,174) and a statistical power of approximately 80%.

## Statistical analysis

The statistical analysis of the primary outcomes and the quantitative variables will be compared using the *F*-test family, specifically the ANCOVA. For secondary outcomes, multivariable regression models will be used to adjust for relevant covariates, including demographic, clinical, and radiological variables associated with both treatment selection and outcomes. We will opt for parametric tests when the samples prove to originate from a population with a normal distribution according to the Kolmogorov–Smirnov test. We will consider *α* = 0.05 to characterize statistical significance. Data analysis and graph creation will be performed using GraphPad Prism version 10.1.1 for Mac, GraphPad Software, Boston, MA, USA, and using IBM SPSS Statistics, version 29.0 - 2022 (IBM Corp., Armonk, NY, USA).

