## Introduction

Among all childhood cancers, central nervous system (CNS) tumors account for 20.7%, second only to leukemias; however, among solid tumors, they are the most common, and of these, infratentorial tumors represent 60% of cases [1]. Posterior fossa tumors are associated with hydrocephalus [2], specifically non-communicating hydrocephalus, since most of these tumors cause direct or indirect obstruction of the fourth ventricle and/or its outflow pathways [3–5].

In a study of 117 children with posterior fossa tumors, Culey et al. [4] reported hydrocephalus in 83% of the patients. Dias MS et al. [5] concluded that one-quarter to one-third of infants with posterior fossa tumors were associated with hydrocephalus requiring diversion.

Although it may be intuitive to think that obstructive hydrocephalus can be treated with tumor resection, several factors predispose to persistent hydrocephalus after tumor removal: young age, preoperative hydrocephalus, midline tumor location, metastases, subtotal resection, tumor pathology, use of external ventricular drains, and postoperative complications [6].

There are several clinical contexts related to the treatment of hydrocephalus secondary to posterior fossa tumors; therefore, various management strategies for hydrocephalus secondary to infratentorial tumors have been described, such as endoscopic third ventriculostomy (ETV), ventriculoperitoneal shunt (VPS), external ventricular drainage (EVD), or direct resection of the lesion without other diversion methods [7–10]. However, each of these strategies has risks and benefits associated with the therapeutic decision made for each patient, and part of the difficulty in choosing a safer treatment method is due to the multiple outcomes selected in studies with different methodologies, making comparison between studies and between hydrocephalus treatment methods very difficult.

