### Outcome assessment

The primary outcome of this study will be the number of reintervention surgeries for the treatment of hydrocephalus after the index surgery for hydrocephalus treatment, which will be chosen at the discretion of each participating center and the attending physician responsible for the patient’s initial treatment.

Patients will be included after signing the Informed Consent Form and/or Assent Form and meeting the inclusion and exclusion criteria. Their data will be anonymously entered into the REDCap software (Fig. 1) for prospective follow-up. Each participating center will be recognized by a specific identifying number. Once the patient is selected to participate in the study, they will be prospectively followed, and each outcome event may be recorded in real time or at the predetermined follow-up times of 1 month postoperatively, 3 months, 6 months, 9 months, and 12 months, always considering day zero as the day on which the hydrocephalus treatment was performed.

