The main limitation of this study will be the lack of randomized treatment allocation. Given the ethical and practical constraints of the clinical setting, randomization was not feasible, which may introduce selection bias. To mitigate this bias, a pre-specified statistical analysis plan was established, including the use of multivariable regression models to adjust for relevant covariates, such as demographic, clinical, and radiological variables associated with both treatment selection and outcomes. In addition, propensity score–based methods will be employed, which may be applied through matching, weighting, or covariate adjustment, depending on statistical appropriateness. Despite these strategies, residual confounding cannot be completely excluded, which remains an inherent limitation of observational studies. Another limitation relates to the use of the operative field quality scale (0–10), which is not a previously validated instrument. This variable was included as an exploratory measure to capture the surgeon’s intraoperative perception of surgical field conditions, which are difficult to quantify using standardized tools. Therefore, its results should be interpreted with caution, and no formal validation or reproducibility testing of this scale was performed.

The present study aims to compare the clinical outcomes associated with the four management strategies analyzed (ETV, VPS, EVD, and primary tumor resection) in a real-world clinical setting. No superiority of any strategy is assumed prior to data analysis, and the study is conducted under the principle of clinical equipoise, with the objective of identifying potential differences in outcomes and contributing to the determination of the most appropriate therapeutic approach.

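### The primary comparison of four physician-chosen treatments is specified with age as its only named covariate, confounder adjustment is assigned to secondary outcomes, and the Discussion's bias-mitigation claim does not say which applies to the primary outcome

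*Protocol article*

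**What the plan says.** All references are to the Protocol article.

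- **Outcome assessment.** The primary outcome is a count: "The primary outcome of this study will be the number of reintervention surgeries for the treatment of hydrocephalus after the index surgery". The index procedure is not randomised but is one "which will be chosen at the discretion of each participating center and the attending physician responsible for the patient’s initial treatment".
- **Sample size calculation.** The primary analytical objective is a comparison of four strategies adjusted for age. The planning model matches it: "The model included four comparison groups and one covariate (age"). The result is 179 participants, about 200 after 10% loss, with F(3,174) and power of about 80%.
- **Statistical analysis.** The primary outcome is given ANCOVA, with no covariates listed in that section. The next sentence reads "For secondary outcomes, multivariable regression models will be used to adjust for relevant covariates", and describes those covariates as ones related to both treatment selection and outcome.
- **Discussion.** "The main limitation of this study will be the lack of randomized treatment allocation". The answer offered is: "To mitigate this bias, a pre-specified statistical analysis plan was established, including the use of multivariable regression models". Propensity-score methods are added, "which may be applied through matching, weighting, or covariate adjustment, depending on statistical appropriateness". No outcome is named for either, and residual confounding is conceded.
- **Introduction.** Factors said to predispose to persistent hydrocephalus after tumour removal include "young age, preoperative hydrocephalus, midline tumor location, metastases, subtotal resection, tumor pathology".

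**The concern.** Variables related to both treatment choice and outcome are confounders. The Statistical analysis section recognises them but attaches adjustment for them to the secondary tier. For the primary outcome the only covariate named anywhere is age. Selection bias is the limitation the authors rank first, and the primary outcome is where it matters most.

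The Introduction names prognostic factors beyond age, such as midline location, metastases and pathology. It is plausible, though the article does not show it, that these also influence which procedure is chosen. If so, an age-only comparison mixes treatment effect with case mix, and a difference between arms could be read as a treatment difference when it is partly a patient difference.

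The Discussion's account of mitigation does not settle this. A reader cannot tell whether the main result will be the age-adjusted ANCOVA, a multivariable model or a propensity-score analysis. These can give different answers, and the propensity variants can also refer to different populations.

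**Working it through.** **1. The plan's own figure.** Inputs from the Sample size calculation section: f = 0.25, α = 0.05, four groups, one covariate. Formula: noncentrality λ = N·f², df1 = 4 − 1 = 3, df2 = N − 4 − 1.

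- At N = 179: λ = 179 × 0.0625 = 11.19, df2 = 174, power 0.801. At N = 178 power is 0.799, so 179 is the minimum and is reproduced.
- 179 / 0.90 = 198.9, so 199, stated as about 200.

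The arithmetic is right, and df2 = 174 corresponds to exactly one covariate.

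**2. The sections side by side.**

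| Section | Primary outcome | Adjustment for treatment-selection variables |
|---|---|---|
| Sample size calculation | four groups, adjusted for age | not mentioned |
| Statistical analysis | ANCOVA, covariates not listed | stated for secondary outcomes |
| Discussion | not named | multivariable and propensity methods, outcome not named, propensity form open |

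The first two rows together give an age-only primary analysis. The third neither confirms nor overrides that.

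**3. What is at stake if the first two rows are followed.** This is an illustration; none of its inputs is in the article. Assumptions: four arms of 45, no treatment effect, negative-binomial counts with dispersion k = 2, mean 0.3 reinterventions without the factor, and one binary prognostic factor with rate ratio RR and arm-specific prevalence p. The arm mean is 0.3 × [1 + p(RR − 1)], so the spurious ratio between extreme arms is [1 + p_max(RR − 1)] / [1 + p_min(RR − 1)].

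| Prevalence by arm | RR | Spurious ratio | Type I error, age only | Age plus factor |
|---|---|---|---|---|
| 40/45/55/60% | 2 | 1.60/1.40 = 1.14 | about 6% | about 5% |
| 30/40/60/70% | 2 | 1.70/1.30 = 1.31 | about 9% | about 5% |
| 30/40/60/70% | 3 | 2.40/1.60 = 1.50 | about 16% | about 5% |
| 20/40/60/80% | 3 | 2.60/1.40 = 1.86 | about 30% | about 5% |

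Repeat runs moved the last two age-only entries within about 15-17% and 29-32%.

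**4. Cost of adjusting.** Same formula as step 1.

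- Ten covariates instead of one, unrelated to treatment: df2 = 165, power 0.801 at N = 179.
- Weighting at an assumed 70% or 80% efficiency of 180 patients: effective N = 126 or 144, power 0.63 or 0.70.
- Regression with ten covariates, where confounders explain an assumed share R² of treatment-group variation, so λ is multiplied by (1 − R²) and no gain from smaller residual variance is credited: at R² = 0.1, 0.2, 0.3, power at N = 179 is 0.75, 0.70, 0.63. For 80% power, N is 198, 223, 254, or 220, 248, 283 after 10% loss.

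**The case against.** The strongest reply is that the Discussion promises multivariable and propensity-score adjustment against selection bias and does not confine it to secondary outcomes. It also refers to a pre-specified analysis plan that is not shown and may assign these methods to the primary outcome. This stands in part. A reader might infer from the Statistical analysis section that the primary result is certain to remain confounded and that the stated mitigation never reaches it. The article does not say so; its sections conflict rather than clearly exclude adjustment. The conflict itself is in the published text, however, because the article names a covariate for the primary comparison and attaches confounder adjustment to other outcomes.

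Other points against a stronger reading also stand:

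- F(3,174) might be taken to leave no room for more covariates. It is a planning figure and does not limit the analysis model; step 4 shows that ten covariates cost almost nothing in degrees of freedom.
- Not every factor in the Introduction's list is a usable confounder. Hydrocephalus is an entry criterion, so its presence cannot differ between arms; only its severity can. Subtotal resection is determined after the index decision. A preoperative histological diagnosis is recorded only if available.
- Leaving the covariate list and technical details of a propensity method to an analysis plan is normal for an article. What remains is that the choice of method is tied to later appropriateness, with no statement that it is fixed before outcomes are analysed.
- The simulated error rates follow from assumed confounder strengths. With mild imbalance the inflation is slight, and several confounders could offset one another as well as accumulate.

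**Conclusion.** The point holds as an inconsistency with consequences for the primary result. The Sample size calculation and Statistical analysis sections together describe an ANCOVA with age as the only named covariate for a non-randomised four-way comparison, and place adjustment for treatment-selection variables with the secondary outcomes. The Discussion claims mitigation without saying that it covers the primary outcome.

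Followed as those two sections are written, the main result would be open to confounding by indication. Under the stated assumptions, type I error would lie between about 6% and about 30% against a nominal 5%, with spurious ratios between extreme arms of about 1.1 to 1.9. The article gives no data on confounder strength, so these figures show a plausible range and do not estimate the bias in this study. The documents do not support saying that the result will be confounded, nor that the sample size was miscalculated.

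**What to change.** In the Statistical analysis section, state that the number of reinterventions is analysed with a confounder-adjusted model. Fix one method, multivariable or propensity-based, as primary before data are analysed; the others become sensitivity analyses. Which method is chosen matters less than fixing it. Then align the Sample size calculation section and the Discussion with that statement.

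Use pre-index variables already recorded: age, lesion topography, tumour size, leptomeningeal spread, imaging severity of hydrocephalus and presenting signs as recorded (Table 1). Add centre as far as feasible: with more than 20 centres and about 200 patients, there are fewer than 200 / 20 = 10 per centre on average. Level of consciousness is among the eligibility signs but is not named in Table 1, so it should be listed only if the form captures it. Exclude post-index items such as extent of resection and adjuvant therapy. Keep the age-only ANCOVA as a sensitivity analysis.

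The change is mainly wording and relies mainly on data already collected. The real cost is precision: power stays at about 0.80 at 179 patients if covariates are unrelated to treatment, but falls to about 0.63-0.70 at an assumed 70-80% weighting efficiency. The stated power should be given again for the adjusted analysis, with its assumption, or the target number reconsidered.

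### The Kolmogorov-Smirnov rule, read as written, removes the age-adjusted ANCOVA that the study was sized for, and no adjusted replacement is named for the count outcome

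*Protocol article*

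**What the plan says.** Under Outcome assessment, the outcome is a count: "The primary outcome of this study will be the number of reintervention surgeries for the treatment of hydrocephalus after the index surgery". The Sample size calculation section is built on it ("The sample size calculation was performed considering the number of surgeries as the primary outcome") and makes adjustment for age part of the primary analytical objective. It uses the G*Power procedure "specifically the ANCOVA option: fixed effects, main effects, and interactions, in an a priori analysis" with f = 0.25, α = 0.05, power 80%, four groups and one covariate. This gives 179 participants and F(3,174), or about 200 after 10% loss.

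The Statistical analysis section first assigns the method: "The statistical analysis of the primary outcomes and the quantitative variables will be compared using the" F-test family, specifically ANCOVA. It then gives multivariable regression to the secondary outcomes. The next sentence is the selection rule: "We will opt for parametric tests when the samples prove to originate from a population with a normal distribution", with Kolmogorov-Smirnov as the criterion. No outcome is exempted, and nothing is named for the case where normality is rejected.

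The Discussion mentions a prespecified plan with multivariable regression and propensity score methods. It does not withdraw the normality rule.

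**The concern.** ANCOVA is a parametric method, so two consecutive instructions bear on the primary outcome: use ANCOVA, and use parametric methods only if the data pass a normality test. A small integer count with many zeros is not normal, so the result of that test is largely known before any patient is enrolled.

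At stake is which analysis is primary. If the rule is obeyed, the sized analysis is dropped and the replacement is chosen after the data are seen. The usual four-group rank test has no covariate term, so it could not deliver the age adjustment in the stated objective. That loss matters in a non-randomised comparison whose authors name selection bias as the main limitation. If the rule is set aside, a common-variance model is fitted to a count whose variance rises with its mean.

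**Working it through.** **1. The plan's own figure.** Inputs from Sample size calculation: f = 0.25, α = 0.05, four groups, one covariate. Noncentrality λ = f²N; df1 = 3; df2 = N − 4 − 1.
- N = 179: λ = 0.0625 × 179 = 11.19, df2 = 174, power 0.8015.
- N = 178: power 0.7989.

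So 179 is the smallest adequate N, and 179/0.9 = 199, or about 200. The sizing reproduces exactly for an age-adjusted ANCOVA.

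**2. How small the count is.** The Discussion gives cumulative failure of 21% (ETV) and 29% (VPS), so 71–79% of those children would have zero reinterventions. Assuming a Poisson count, mean = −ln(1 − failure proportion):
- ETV: −ln(0.79) = 0.24
- VPS: −ln(0.71) = 0.34

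The article gives no such rates for EVD or resection, so other means below are assumptions.

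**3. Kolmogorov-Smirnov by hand.** Compare the proportion of zeros with the value at zero of a normal distribution having the same mean m and variance m, which is Φ(−√m).
- m = 0.24: 0.79 − 0.31 = 0.48
- m = 0.34: 0.71 − 0.28 = 0.43

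The 5% critical distance for the uncorrected test is about 0.20 at n = 45, 0.19 at n = 50 and 0.10 at n = 179. The discrepancy is more than twice the limit even in the smallest group.

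**4. Simulated rejection rates (Poisson).**

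| Mean | n | Uncorrected | Lilliefors-corrected |
|---|---|---|---|
| 0.24 and 0.34 | 45, 50, 179 | 100% | 100% |
| 1.0 (assumed) | 45–179 | at least 98% | 100% |
| 2.0 (assumed) | 45–50 | about 46–58% | 99.9–100% |
| 2.0 (assumed) | 179 | 100% | 100% |

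Testing ANCOVA residuals (N = 179) instead of raw counts also gives 100% when the group means are built on the 21% and 29% rates. With assumed group means of 0.66 to 1.34, it gives 99.6% (corrected) and 86% (uncorrected).

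**5. If the rule does not apply to the primary outcome.** With 45 per group, the ANCOVA omnibus type I error was 0.048–0.058 (common mean 0.3, Poisson or overdispersed). Power at f = 0.25 was 0.80–0.86. Unadjusted Kruskal-Wallis had power 0.77–0.85 in the same settings.

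**6. Common variance and intervals.** Take one arm with mean a and three with mean b, equal sizes, Poisson. The pooled variance is (a + 3b)/4. The interval for a − b uses 2 × pooled variance where the true value is a + b.
- a = 0.34, b = 0.24: pooled 0.265; √(0.53/0.58) = 0.956; coverage 2Φ(1.96 × 0.956) − 1 = 94%.
- a = 0.8, b = 0.3 (assumed): pooled 0.425; √(0.85/1.10) = 0.879; coverage 2Φ(1.96 × 0.879) − 1 = 91.5%.

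Simulation with 45–50 per arm gives about 94% and 91%. With overdispersed counts (negative binomial, size 1), the second case falls to about 90%.

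**The case against.** The strongest reply is about scope. The section opens by giving the primary outcome to ANCOVA without condition, and the normality sentence comes after the one on secondary outcomes. It may be boilerplate for other quantitative variables. That reading is possible, but the text does not say so: the rule refers to the samples without limit, and the opening sentence groups the primary outcomes with the quantitative variables. The two sentences need reconciling either way.

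A second reply is that the analysis plan mentioned in the Discussion will settle the matter. Detail left to that plan is no finding. Here, though, the article states a method and a rule that conflict, and the Discussion does not lift the rule.

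A third reply is that ANCOVA is robust. For the omnibus test this stands: its error rate is about nominal and its power is close to plan.

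Four stronger readings are tempting and are not supported:
- *The plan ends in an unadjusted Kruskal-Wallis test.* No fallback is named; that is only what usually follows.
- *Neither route matches the sample-size model.* If the rule is set aside, the analysis is exactly the ANCOVA that was sized.
- *Intervals are badly wrong for the arm that differs most.* Coverage near 83% needs an arm of 20 among 180 at assumed means of 0.8 versus 0.3. The Abstract says each group will include at least 50.
- *The rule fails whatever the data.* Uncorrected Kolmogorov-Smirnov applied per group would often pass at means near 2.

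**Conclusion.** The concern holds in a limited form. As written, the rule selects the primary method by a test whose result is practically certain at the article's own failure rates. It then discards the age-adjusted ANCOVA and names no adjusted alternative. That conclusion rests on a Poisson conversion of the 21% and 29% rates and on assumed means for EVD and resection.

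On the narrower reading, in which the rule does not reach the primary outcome, the remaining weakness is modest: interval coverage of about 94% at the article-based means and about 90–91% at the assumed wider contrast. The sample size and the omnibus error rate are not materially affected on that reading. This should be fixed before outcomes are analysed, but it does not undermine the design.

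**What to change.** Remove the normality rule for the primary outcome. Prespecify one adjusted count model: negative binomial or quasi-Poisson, log link, robust standard errors, arm as a four-level factor, with age and the baseline covariates. Report adjusted rate ratios and adjusted mean surgeries per child with 95% intervals.

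At minimum, state that the adjusted model is used whatever the Kolmogorov-Smirnov result, with robust standard errors.

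The cost is wording; the named software's generalised linear model procedure covers such models. The power cost is a few points at most: in simulation at assumed means of 0.2, 0.3, 0.4 and 0.6, quasi-Poisson had 62% power, ANCOVA 66% and Kruskal-Wallis 61%.
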